### Sample size and statistical analysis

#### Statistical analysis

The per-patient PCa detection rates of both targeted biopsy regimens will be tested separately for non-inferiority against current standard 12-core systematic biopsies using a one sided non-inferiority test for correlated proportions [22, 23]. To evaluate if image- targeted biopsies can be used complementarily, we will also perform the same comparative analysis for the targeted biopsy results combined, compared to the systematic biopsies. Moreover, the per-patient CDR’s of all three biopsy protocols will be directly compared using McNemars test for correlated proportions. The same analyses will be performed including all tumors and including clinically significant tumors only, defined as PCa with a Gleason score ≥3 + 4 = 7.

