#### Sample size calculation

The sample size calculation is based on the non-inferiority test between the targeted biopsy procedures and the systematic biopsies. For this test we performed a power analysis, with the detection rate for systematic biopsies set at 45% [24], a power of 80% and the significance level (alpha) of 5%. The maximum allowable difference in detection rate for the targeted biopsies to be considered non-inferior to systematic biopsies was set at 1%. We expect a maximum proportion of discordant pairs of 15% and a detection rate difference of 5%. The required sample size according to these specifications is 260 patients. Based on the estimation that 15% of the patients that are scheduled for biopsies will not receive targeted biopsies due to the absence of PCa suspected lesions on imaging; a total number of 299 patients will be enrolled in the study.

Literature shows that of all positive biopsies about 25% is Gleason >6 [25–27]. Results from our institution differ from literature as only 40% of all the patients with PCa at biopsy have a Gleason score 6 PCa, while 60% of them have a Gleason score >6 PCa. Thus, numbers of positive biopsies and Gleason score > 6 are higher than reported in literature. Based on our historical data we expect that by including 299 patients in the study we will find ~65 cases with a Gleason score = 6 and ~100 cases with a Gleason score > 6. For differentiation between Gleason score we hypothesize that we need at least 40 people in both Gleason grade groups.

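### Enrolment of 299 is 260 × 1.15; a 15% loss needs 260 / 0.85 = 306, so 299 leaves about 254 men against the 260 the plan requires

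*Protocol article*

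**What the plan says.** The Statistical analysis section of the protocol article tests each targeted regimen against 12-core systematic biopsy with a "one sided non-inferiority test for correlated proportions". The Sample size calculation section gives the inputs: 45% detection with systematic biopsy, 80% power, 5% alpha, a 1% margin, at most 15% discordant pairs and an expected difference of 5%. It then states: "The required sample size according to these specifications is 260 patients".

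The next sentence allows for men who will have nothing to target. It estimates that "15% of the patients that are scheduled for biopsies will not receive targeted biopsies due to the absence of PCa suspected lesions on imaging", and on that basis "a total number of 299 patients will be enrolled in the study". The figure of 299 is repeated in the Abstract and under Population. The second paragraph of the sample size section also builds its expected Gleason counts on it.

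**The concern.** The 15% is defined as a share of the men scheduled for biopsy, and the Population section enrols exactly such men. A loss stated as a fraction of those enrolled is allowed for by dividing the required number by one minus that fraction. Multiplying the required number by one plus the fraction gives too few, and 299 is exactly what that multiplication produces.

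If so, three figures in adjacent sentences (260, 15% and 299) cannot all be right, and the headline size of the trial does not secure the number of paired comparisons on which its 80% power rests.

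**Working it through.** **Inputs** (Sample size calculation, with the test from Statistical analysis): one-sided α = 0.05, power 80%, discordance ψ = 0.15, expected difference d = 0.05 in favour of targeted biopsy, margin m = 0.01, required n = 260, loss 15%, enrolment 299. The 45% systematic detection rate is not needed once ψ and d are fixed.

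**Step 1. Reproduce 260.** For a paired non-inferiority score test with null variance V₀ from restricted maximum likelihood,

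n = (z₀.₉₅ √V₀ + z₀.₈₀ √V₁)² / (d + m)²

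- V₁ = ψ − d² = 0.15 − 0.0025 = 0.1475, so √V₁ = 0.3841.
- Under the null the discordant probabilities differ by the margin. The restricted estimates are 0.0817 (systematic positive only) and 0.0717 (targeted positive only). V₀ = 0.0817 + 0.0717 − 0.01² = 0.1532 (from unrounded values), so √V₀ = 0.3914.
- n = (1.645 × 0.3914 + 0.8416 × 0.3841)² / 0.06² = 0.9352 / 0.0036 = 259.8, or **260**.

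This matches the plan exactly. Simpler formulas come close: using ψ as the variance gives 258, and using ψ − d² throughout (Wald) gives 254. A one-sided α of 0.025 gives 322 to 331 and does not match.

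**Step 2. Reproduce 299.** 260 × (1 + 0.15) = 299.0 exactly.

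**Step 3. Enrolment that leaves 260 after a 15% loss.** 260 / (1 − 0.15) = 305.9, or **306**, which is 7 more than 299.

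**Step 4. What 299 delivers.** 299 × 0.85 = 254.15, or **254** men, 6 fewer than 260. Put the other way, 299 covers a loss of 1 − 260/299 = 13.0%, not 15%.

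**Step 5. Power**, from Φ{[(d + m)√n − z₀.₉₅ √V₀] / √V₁} for the score method and the corresponding expressions for the other two:

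| Men compared | Score | ψ variance | Wald |
|---|---|---|---|
| 254 | 79.2% | 79.5% | 80.1% |
| 260 | 80.0% | 80.3% | 80.9% |
| 299 | 84.7% | 84.9% | 85.5% |
| 306 | 85.5% | 85.7% | 86.2% |

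The loss from 260 to 254 is 0.8 points by each method. The rows for 299 and 306 apply only if nobody is lost.

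**The case against.** The division slip itself is hard to dispute; the case on the other side concerns its weight and its conditions.

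- **It is negligible.** Seven men are 2.3% of the corrected 306, and the power cost is under one point. The plan calls its 15% discordance a maximum, and 254 men give 80% power once discordance is about 14.7% or lower. This stands as a statement of size. It does not make the printed figures agree.
- **The power claim depends on the method.** By the Wald formula 254 men give 80.1%, and 254 / 0.85 = 298.8 also rounds up to 299, so a requirement of 254 would have been met. That is true, but the plan prints 260, which the score method reproduces exactly. The shortfall against 260 remains; power at 254 is fairly described as 79% to 80%.
- **The article never says that men without targets leave the analysis.** The detection rates are per patient, no exclusion is named, and the expected Gleason counts are projected from all 299. If these men count as negative on targeted biopsy, all 299 are analysed and there is no shortfall. This is the strongest point, and it makes the figure of 254 conditional. Yet on that reading 260 enrolled would already give 260 analysed and the inflation would serve no purpose. The 5% difference and 15% discordance would also have to describe the whole population, including men with nothing to target. The sentence needs correction on either reading.

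**Conclusion.** The concern holds. On the plan's own figures, enrolment should be 306, not 299; 299 leaves about 254 men for the paired comparison, 6 below the stated requirement. Power falls from 80.0% to 79.2% by the method that reproduces 260. This is a small arithmetic error in the stated size of the trial and does not make it materially underpowered.

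The conclusion rests on two readings of the article: that the 15% is a share of the men enrolled, as its wording says, and that men without targeted biopsies are lost to the comparison, which is the only reading under which the inflation makes sense. The article gives a single 15% for imaging as a whole. If that means no lesion on either modality, the share without a target for one given modality is at least as large, and each separate comparison would have 254 men or fewer. The article does not settle this, and the arithmetic finding does not depend on it.

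**What to change.** Correct the last sentence of the first paragraph under Sample size calculation, in one of three ways:

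1. Give 306 as the enrolment implied by 260 and a 15% loss, and change 299 wherever it appears, including the Abstract, Population and the basis of the Gleason projections. This costs 7 more men.
2. Keep 299, and state that about 254 men are expected to be evaluable, with about 79% power by the method that gives 260. This costs one sentence and a slightly less favourable figure.
3. If men without targets are to be counted as negative on targeted biopsy, say so, remove the 15% inflation, and restate the calculation on all 299 with a difference and discordance that describe that full population. This needs no extra enrolment, but both inputs must be reconsidered.

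Whichever is chosen, the section should state how men without targeted biopsies enter the comparison, because that decides which correction applies.

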### Quality and patient safety

The quality of the data obtained and patient safety will be continuously monitored by the investigators. Periodical (yearly) reporting of study progression and patient safety will be performed to the reviewing Institutional Review Board (IRB). In accordance to section 10, subsection 4, of the Wet Medisch-Wetenschappelijk Onderzoek met Mensen (Medical Research Involving Human Subjects Act), the investigators will suspend the study if there is sufficient ground that continuation of the study will jeopardise subject health or safety. The investigators will notify the accredited IRB without undue delay of a temporary halt including the reason for such an action. The study will be suspended pending a further positive decision by the accredited IRB. The investigator will take care that all subjects are kept informed.

#### Risks and benefits

The mpMRI and TRUS - guided prostate biopsies are already performed routinely in our institution. The extra targeted prostate biopsies are considered to convey minimal additional risk over the systematic biopsy cores that were already planned. When contraindications for mpMRI and necessary preparations for prostate biopsies (proper antibiotic prophylaxis and management of anticoagulant medications) are followed, these investigations are considered safe [3]. After use in thousands of patients, adverse events related to micro bubble UCA’s appear to be transient, mild and rare [28–30]. The most frequent minor side-effects are a transient alteration of taste, local pain at the injection site and facial or general flush (1–5%) [31]. Serious adverse events, which consists of hypersensitivity allergic reactions, are rare (<0.01%) [32]. In a study with SonoVue® in patients with chronic obstructive pulmonary disease, CEUS appeared to be as safe and well tolerated as in a healthy control group [28]. The Committee for Medicinal Products for Human Use has granted SonoVue® a marketing authorization, but it should not be used together with the medicine dobutamine and in pregnant or breastfeeding women (http://www.ema.europa.eu). Although patients are informed about the experimental nature of CEUS imaging, a potential benefit of participation is the real possibility of finding (significant) PCa in one of the targeted biopsies that would otherwise have remained undetected.

## Discussion

Improvement of the PCa diagnostic pathway is necessary, and will likely depend on the advances in PCa imaging. Multiparametric MRI has a recognized value before a second biopsy in case of a persistent clinical suspicion for PCa. The value in biopsy - naïve patients and the possibility to omit systematic biopsies is debated [3]. Contrast -enhanced ultrasound has shown promising results, but should currently be viewed as experimental. This trial will provide data on both these techniques, allowing comparison and assessment of complementarity. The study design chosen is in line with recommendations formulated by the Standards of reporting for MRI-targeted biopsy studies (START) Working Group [33] and by van Hove et al [9]. To validate imaging - targeted prostate biopsy protocols van Hove et al. recommend using either one of two study designs: randomize patients to undergo either systematic biopsies alone or systematic biopsies and targeted biopsies. In the other option every patient undergoes both targeted biopsies and systematic biopsies by separate blinded observers. In our study design all patients undergo both imaging procedures and both targeted and systematic biopsies. The targeted biopsies and systematic biopsies are performed by separate observers. The targeted biopsy locations are predetermined by blinded readers and targeted through a fusion device. To prevent potential bias by post-biopsy haemorrhage seen on ultrasound the targeted biopsies are performed after the systematic biopsies. This way we prevent information gathered from one imaging technique to influence biopsy targeting for the other imaging technique. In both study designs the (significant) PCa detection rates are compared. An advantage of using these study designs is that there is no spectrum bias, i.e. the relevant biopsy population is being studied. Also, there is no observer bias, the investigator reading the images does not already know that there must be a tumor. Both spectrum bias and observer bias occur when translating results obtained from the correlation of imaging and radical prostatectomy specimens towards the primary diagnostic setting. Furthermore, the endpoint in this study design, (significant) PCa detection, is the most relevant endpoint in the clinic. We therefore believe that our trial will provide important and necessary data on one of the most relevant topics in PCa care. This data is gathered in a recommended, standardized fashion to minimize bias and allow data pooling.

## Abbreviations

(mp)MRI: (multiparametric) Magnetic Resonance Imaging
AUC: Area Under the Curve
CDR: Cancer Detection Rate
CEUS: Contrast - Enhanced Ultrasound
CUDI: Contrast Ultrasound Dispersion Imaging
DRE: Digital Rectal Examination
EAU: European Association of Urology
IDM: Interdepartmental Monitoring
IRB: Institutional Review Board
PCa: Prostate Cancer
PSA: Prostate Specific Antigen
TIC: Time-Intensity-Curve
TRUS: Transrectal Ultrasound
UCA: Ultrasound Contrast Agent
